*Data collection and screening algorithm*. For each Index case, socio-demographic information and results from their Acid-fast bacilli (AFB) smear and/or Xpert MTB/RIF testing at the CHC or hospital will be obtained. Sputum samples will be sent to the research laboratory for culture and storage. From each consenting household contact a symptom screen will be undertaken (Fig 2) as well as enquiry about any history of TB, whether they are on any TB preventive therapy, have any other immunocompromised medical condition, and their socio-demographic information (age, gender, ethnicity, smoking status). The location of each household will be recorded using an electronic geographic coordinate system. Any person with symptoms suggestive of TB (weight loss, night sweats, fever, chest discomfort or pain) will undergo clinical assessment. Any person with a productive cough of any duration will be asked to provide two sputum samples for AFB smear and/or Xpert MTB/RIF testing, and *Mtb* culture [17, 18]. All participants will be offered a chest x-ray, followed by sputum examination if the x-ray has changes suggestive of TB. Chest x-ray reports will be read by a radiologist. Cases with a radiology report showing indication of TB without bacteriology positivity will be consulted to an infectious disease specialist to determine whether they should receive TB treatment or not. All diagnostic procedures and treatment for any person found to have TB will be undertaken according to National TB guidelines.

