### Outcome measures and statistical analysis

We will categorize TB for Index and household/neighbourhood contacts into four categories: definite TB, probable TB, possible TB, and not TB. Subjects are categorised as definite TB if their *Mtb* culture or Xpert MTB/RIF positive; probable TB if they have TB symptoms, chest x-ray suggestive of TB, and AFB smear-positive but culture negative/not done; possible TB if they have TB symptoms and/or chest x-ray suggestive of TB but all bacteriology examinations negative/not done; and not TB if there was no evidence of TB on a symptom review or investigations. Chest x-rays will be classified as normal, suggestive active TB, suggestive inactive TB, or abnormal not TB based on the radiology report.

The key outcomes of this study are to estimate the TB prevalence and incidence in neighbourhoods around known TB cases, compared to households of known TB cases. TB prevalence defined as the number, percent and 95% confidence intervals (CI) of positive TB cases, according to each TB definition (definite, probable, possible), will be estimated. These proportions will be compared between households, neighbourhoods, and estimates from the Indonesian National Prevalence Survey for Java/Bali. TB incidence defined as incidence rates and 95% CI of positive TB cases according to each TB definition (definite, probable, possible), will be calculated per 1000 person-days. Person-days will be calculated as the days from the date of baseline examination to either: a) the date of TB diagnosis, b) date of death (if died) as reported by household member, c) date of 12-month follow-up examination, or d) date left the neighbourhood area for any household member who has left the area before the 12-month follow-up.

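### The four TB categories neither cover every result nor exclude one another, and possible TB can be met by symptoms alone, so the possible and probable estimates are unreliable while definite TB stands

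*Protocol article*

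**What the plan says.** In the protocol article, Outcome measures and statistical analysis, contacts and Index cases are sorted "into four categories: definite TB, probable TB, possible TB, and not TB".

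- Definite: "culture or Xpert MTB/RIF positive".
- Probable: "probable TB if they have TB symptoms, chest x-ray suggestive of TB, and AFB smear-positive but culture negative/not done".
- Possible: "possible TB if they have TB symptoms and/or chest x-ray suggestive of TB but all bacteriology examinations negative/not done".
- Not TB: "not TB if there was no evidence of TB on a symptom review or investigations".

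The same section names prevalence and incidence as key outcomes. It reports positive cases separately under the definite, probable and possible definitions, and compares the prevalence proportions between households, neighbourhoods and the national prevalence survey.

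The screening rules are in 1) Prospective cohort study, under data collection. On symptoms: "Any person with symptoms suggestive of TB (weight loss, night sweats, fever, chest discomfort or pain) will undergo clinical assessment". On sputum: "Any person with a productive cough of any duration will be asked to provide two sputum samples". X-ray is offered to all, and suggestive changes also lead to sputum examination. People with a suggestive x-ray and no positive bacteriology "will be consulted to an infectious disease specialist to determine whether they should receive TB treatment or not". X-rays are recorded in four classes, which separate suggestive active from suggestive inactive TB, but the case rules do not use that split.

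**The concern.** A graded case definition should give each person exactly one place, and each counted grade should mean some degree of TB. Neither holds here.

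First, the and/or in the possible rule makes symptoms sufficient. Fever or chest discomfort with a normal x-ray and negative sputum qualifies. So does weight loss with no sputum taken. Such a person cannot be not TB, because that category requires a clear symptom review.

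Second, the probable rule requires three findings together, while the possible rule bars any positive bacteriology. A smear-positive person who has only some of the three findings falls between them. The probable rule also does not exclude a positive Xpert, so it overlaps with definite.

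At stake are the possible and probable estimates of prevalence and incidence and their comparison with the survey. Incidence is touched at both ends. Follow-up covers people without evidence of TB at baseline, so symptom-only people could be left out of it, and the 12-month visit is described as a repeat symptom screen, so a new symptom could read as an incident possible case.

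**Working it through.** **1. The plan's own figure.** From Sample size, Prevalence in neighbourhoods: p = 0.0125 (culture-positive), n = 4500. The Wald interval is p ± 1.96 × √(p(1 − p)/n) = 0.0125 ± 1.96 × √(0.0125 × 0.9875/4500) = 0.93% to 1.57%. This rounds to the stated 0.9% to 1.6%. The figure is sound, and it concerns culture-positive TB, which lies within definite.

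**2. Do the categories cover everyone once?** Take symptoms (yes/no), x-ray (suggestive, not suggestive, not done), and smear, culture and Xpert (each positive, negative, not done). That gives 2 × 3 × 3 × 3 × 3 = 162 profiles. Each was tested against the four rules as written, with any positive smear counted as evidence of TB.

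The gap arises when smear is positive, culture is negative or not done (2 options) and Xpert is negative or not done (2 options), giving 4 bacteriology patterns. Of the 6 symptom and x-ray combinations, only symptoms plus a suggestive x-ray reaches probable. The other 5 reach nothing:

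| Symptoms | X-ray | Combinations | × 4 patterns |
|---|---|---|---|
| Yes | Not suggestive or not done | 2 | 8 |
| No | Suggestive | 1 | 4 |
| No | Not suggestive or not done | 2 | 8 |
| Total | | 5 | 20 |

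Two profiles meet both definite and probable: symptoms, suggestive x-ray, smear-positive and Xpert-positive, with culture either negative or not done. No culture-positive or Xpert-positive profile is left out of definite.

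**3. Can the gap be reached?** Yes. Sputum is requested for productive cough whatever the x-ray shows, and for x-ray changes whatever the symptoms. Smear and Xpert are joined by and/or, so Xpert may not be done. The third row depends on whether productive cough itself counts as a TB symptom, which the text does not settle.

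**4. Does screening produce symptom-only cases?** Yes. For a person with night sweats, no productive cough and a normal x-ray, the text describes clinical assessment but no sputum request. If none is taken, bacteriology is not done and the possible rule is met. If sputum is taken and is negative, the rule is still met.

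**5. Size.** The article gives no symptom frequency, so the share s of neighbours who have symptoms, no suggestive x-ray and negative or no bacteriology is an assumption. Expected culture-positive neighbours: 4500 × 0.0125 = 56.25, about 56. Symptom-only possible cases: 4500 × s.

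| s (assumed) | Symptom-only possible cases | s ÷ 1.25% | s ÷ 0.5% survey figure |
|---|---|---|---|
| 2% | 90 | 1.6 | 4 |
| 5% | 225 | 4 | 10 |
| 10% | 450 | 8 | 20 |
| 15% | 675 | 12 | 30 |

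Numerator and comparator both refer to the 4500 neighbours.

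**The case against.** The best defence is that the three definitions are reported separately. A weak possible grade cannot contaminate definite, and both the sample-size target and the genomic component rest on culture. That stands. A reader might infer that every reported prevalence will be wrong; the rules do not support this, since the definite rule captures every culture-positive or Xpert-positive profile and the target interval reproduces.

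It can also be said that Figures 2 and 3 are not shown and might set a symptom threshold, and that the symptom list in the text governs clinical assessment and is not offered as the definition of TB symptoms. This limits certainty about how many people qualify. It does not remove the and/or, which lets symptoms suffice whatever threshold applies.

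The smear-positive gap is probably a small cell, because culture is planned on sputum and Xpert is available. That also stands, but the gap remains a drafting error in an outcome definition.

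A reader might go further and argue that people who decline x-ray are classed as not TB, and that this biases the household and neighbourhood comparison. The article does not say that uptake differs, any size would rest wholly on assumed refusal rates, and handling of missing examinations is something a condensed article may leave to the full protocol or analysis plan. That is not part of this point.

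**Conclusion.** The point holds for the possible and probable categories. As written, possible TB includes people whose only finding is symptoms. In addition, 20 of 162 profiles, all smear-positive, have no category, and 2 have two. The prevalence and incidence estimates for these two grades, and their comparison with the survey, are therefore unreliable.

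The larger effect is on possible TB: at an assumed 2% to 15% of neighbours, symptom-only cases would number 1.6 to 12 times the expected culture-positive cases. The direction follows from the wording; the size rests entirely on the assumed frequency and on no threshold being set in the figures not shown. The loss from probable is probably small and cannot be sized from the article. Definite TB and the 1.25% target stand.

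**What to change.** Reword the outcome classification, leaving clinical assessment and treatment as they are:

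1. State that definite takes precedence over the other categories. This removes the overlap.
2. Assign every smear-positive result without a positive culture or Xpert to a named category, whatever the symptoms or x-ray show. Relaxing probable to symptoms or a suggestive x-ray would not be enough: the 8 profiles with neither would still have no place.
3. Require an x-ray in the recorded suggestive active class for a counted possible case, and report symptom-only people separately. The specialist's opinion is sought on whether to treat, so it should not be taken as a ready-made diagnostic class.
4. Restrict the survey comparison to bacteriologically confirmed TB.

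The cost is a rewritten paragraph and one extra row in the tables; all inputs are already collected. The downside is fewer possible cases. The change should be made before results are tabulated, since narrowing the definition afterwards would be post hoc.

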**Methods and analysis:**

Individuals (~1000) living in the same household as a case diagnosed with pulmonary TB (n = 250) or in a neighbouring household (~4500 individuals) will be screened for TB symptoms and by chest x-ray. Two sputum samples will be collected for microbiological analysis from anyone with a productive cough. Any person found to have TB will be treated by the National TB Control Program. All those with no evidence of TB disease will have a repeat screen at 12 months. Whole-genome sequencing (WGS) and social network analysis (SNA) will be conducted on Index cases and contacts diagnosed with TB.

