**Fig 2 pone.0256043.g002:**
[figure not shown]
Baseline screening algorithm.

*Follow-up*. All participants with no evidence of TB at baseline will be contacted by phone approximately four-monthly to ask whether they have been diagnosed with TB in the interim. Also, to enable the study team to capture the sputum sample and obtain a culture at the time of diagnosis, household contacts will be given a referral card with the study contact details they can show to any CHC or hospital should they present with any TB symptoms or undergo any TB related diagnostic tests. At 12 months a repeat in-person symptom screen will be done (Fig 3). If an individual within a household leaves the neighbourhood area and cannot be followed-up, the approximate date they left will be ascertained from other household members. If a whole household leaves the area before the 12-month follow-up and are unable to be contacted, an approximate date will be confirmed from neighbours.

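### Symptom-free participants who decline the offered chest x-ray are classed as not having TB, which biases prevalence downwards by an amount that depends on uptake

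*Protocol article*

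**What the plan says.** The paragraph on data collection and the screening algorithm (Prospective cohort study) gives two routes to sputum. One is cough: "Any person with a productive cough of any duration will be asked to provide two sputum samples". The other is the film: "All participants will be offered a chest x-ray, followed by sputum examination if the x-ray has changes suggestive of TB". People with other suggestive symptoms go to clinical assessment. The Abstract describes the same people more firmly, as those who "will be screened for TB symptoms and by chest x-ray".

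Outcome measures and statistical analysis sets four classes: definite, probable, possible and not TB. The third is "possible TB if they have TB symptoms and/or chest x-ray suggestive of TB but all bacteriology examinations negative/not done", so missing bacteriology is provided for. The last is "not TB if there was no evidence of TB on a symptom review or investigations". No minimum work-up is attached to it, and there is no class for people whose screening is incomplete.

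For follow-up, "All participants with no evidence of TB at baseline will be contacted by phone approximately four-monthly". Later, "At 12 months a repeat in-person symptom screen will be done". The incidence clock starts at the first visit: "Person-days will be calculated as the days from the date of baseline examination".

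**The concern.** Read together, these rules treat the absence of a test as the absence of disease. A participant who reports no symptoms and declines the film has no route to sputum. That person meets none of the first three definitions and falls into the fourth. The person then stays in the prevalence denominator as a non-case and enters the incidence cohort on the same footing as someone cleared by x-ray.

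The key outcomes are prevalence and incidence in neighbourhoods compared with households, and prevalence is also compared with the National Prevalence Survey. The sample size section ties a policy change to about 1.25% in neighbourhoods. Undetected cases lower the study's side of the survey comparison and pull the estimate below the planning value, even if uptake is the same in both groups. Unequal uptake would also move the household-neighbourhood ratio.

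**Working it through.** **The plan's own figure.** Sample size gives 95% limits of 0.9 to 1.6% around 1.25% with 4500 neighbourhood participants. The Wald interval is 1.25% ± 1.96 × √(0.0125 × 0.9875 / 4500) = 1.25% ± 0.325%, or 0.93 to 1.57%. This reproduces the stated limits after rounding. The arithmetic is sound, but it presumes that every prevalent case is detected.

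**Inputs.**
- True neighbourhood prevalence 1.25% and N = 4500, from Sample size. Expected cases: 4500 × 0.0125 = 56.25.
- *u*, the x-ray uptake. Not in the document; assumed 0.9, 0.7 or 0.5.
- *s*, the share of prevalent cases detectable by symptoms alone. Not in the document; assumed 0.4 to 0.6.
- Uptake is taken as unrelated to disease status, and symptomatic or x-rayed cases are taken as always detected.

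**Formulas.** Observed prevalence = 1.25% × [u + (1 − u) × s]. Missed cases = 56.25 × (1 − u) × (1 − s).

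| Uptake | Observed, s = 0.4 | Observed, s = 0.6 | Missed of 56 |
|---|---|---|---|
| 90% | 1.175% | 1.20% | 2.3 to 3.4 |
| 70% | 1.025% | 1.10% | 6.8 to 10.1 |
| 50% | 0.875% | 1.00% | 11.3 to 16.9 |

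**Against the survey.** In the lowest cell, the interval is 0.875% ± 1.96 × √(0.00875 × 0.99125 / 4500) = 0.875% ± 0.272%, or 0.60 to 1.15%. Its lower end meets the survey's upper limit of 0.6%. In the 90% row the estimate stays well inside the stated 0.9 to 1.6%.

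**Household-neighbourhood ratio.** Assuming the same *s* in both groups, the true prevalence ratio is multiplied by [u_H + (1 − u_H)s] / [u_N + (1 − u_N)s].
- Equal uptake: multiplier 1.
- 90% in households, 70% in neighbourhoods: 0.94/0.82 = 1.15 (s = 0.4) or 0.96/0.88 = 1.09 (s = 0.6).
- The reverse: 0.82/0.94 = 0.87 or 0.88/0.96 = 0.92.

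**Incidence.** At 70% uptake, 7 to 10 missed neighbourhood cases enter the at-risk cohort. If every one were diagnosed within the year, they would add about 6.75/4500 to 10.1/4500, or 150 to 225 per 100,000. This is a ceiling, because a missed case counts only if it is diagnosed during follow-up.

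**The case against.** The article never mentions decliners. Their class is inferred from a sentence that may simply be loose, and the baseline and follow-up algorithms are in Figs 2 and 3, which were not available for this review. Weighting, uptake tables and sensitivity cohorts commonly belong in a full protocol or analysis plan, so their absence from an article is not a fault. That last point stands, and the finding does not rest on it. It rests on the printed four-class definition, which provides for missing bacteriology but not for a missing film and leaves a symptom-free decliner no other class. If the figures say otherwise, the definition must be made to agree with them.

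It is also fair to say that these participants are not wholly unscreened: they have had a symptom review, and people with symptoms other than productive cough do get clinical assessment. The gap is confined to symptom-free people without a film.

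A reader might infer more than the document supports:
- **That incidence is inflated by the full number of missed cases.** The 12-month visit is described as a symptom screen, so cases that stay symptom-free may never be counted. Setting the missed cases against the feasibility study's 675 per 100,000 per year would also mix definitions: that rate is self-reported TB, while the 1.25% is culture positive.
- **That households will look worse than neighbourhoods.** Household contacts know they live with a patient and neighbours are not told, but nothing shows how this affects uptake. The ratio can move either way.
- **That the survey comparison fails.** Even in the lowest cell the interval only touches 0.6%. The article also does not describe the survey's own screening, so the net bias in that comparison cannot be determined.

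**Conclusion.** The point holds as a flaw in a stated outcome definition. The direction for prevalence is clear: it is underestimated in any group where some symptom-free people have no film. The size is conditional on assumed uptake and symptom-detectable share. It is slight at 90% uptake (about 2 to 3 of 56 neighbourhood cases) and material at 50% (about 11 to 17 of 56, with observed prevalence of 0.88-1.00% instead of 1.25%). Distortion of the household-neighbourhood comparison requires unequal uptake, or a different symptom-detectable share in the two groups, and its sign is unknown. The incidence effect is possible but bounded above by the number missed. The definition should be corrected before uptake is known, so that the handling of decliners is not chosen after seeing the data.

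**What to change.** In Outcome measures and statistical analysis:
- Reserve the not-TB class for people with a negative symptom review and either a completed x-ray that is not suggestive of TB or, where there is no film, negative sputum. A suggestive film with negative sputum stays possible TB, as now.
- Code symptom-free people without an x-ray as incompletely screened. This changes only their analysis label, not who is screened or followed.
- Report x-ray uptake separately for households and neighbourhoods.
- Alongside the crude prevalence, give an estimate that uses inverse-probability weighting or multiple imputation for the missing x-ray, with the covariates already collected: age, sex, smoking, TB history and group.
- Add an incidence sensitivity analysis limited to people x-rayed at baseline. It is better as a sensitivity analysis than as the main one, because restricting the cohort selects on willingness to be x-rayed.

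The cost is a few sentences and modest extra analysis on data already collected. The adjusted prevalence rests on a missing-at-random assumption for uptake given those covariates, and the incidence sensitivity analysis has a smaller denominator.

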## Introduction

Tuberculosis (TB) remains a leading cause of infection globally, with an estimated 10 million new cases of disease and 1.2 million deaths from TB in 2019 [1]. To eliminate TB, we need to identify target populations most at risk so that enhanced intervention can drive the incidence of TB down across the wider population. Many attempts to intensify TB control efforts have focused on TB households [2–4]. However, we now know that in most high burden settings, the majority of *Mycobacterium tuberculosis (Mtb)* transmission occurs in the community where there are vastly greater numbers of human encounters [5] that often share socio-economic risk factors that are correlated with TB [6, 7]. In a feasibility study in Bandung, Indonesia [8] we followed individual TB patients back to their communities. We found an incidence rate of self-reported TB of 649 per 100,000/year in TB household contacts, 675 in neighbouring households, and 325 in randomly selected neighbourhoods [8].

TB disease occurs through two distinct mechanisms (primary progression and reactivation) that require different interventions. Soon after exposure to *Mtb*, a small proportion of people develop TB disease (primary progression) and approximately 50% of them are latently infected but remain well. Of these latently infected people, 5% develop TB disease during their lifetime (reactivation) [9–11]. Early diagnosis and six months of multi-drug treatment of TB disease reduces transmission to case contacts, and preventive treatment of latent TB for as little as three months reduces reactivation in infected contacts by up to 90% [12, 13]. Both strategies are essential for TB elimination [14]. If neighbourhoods around TB cases have high rates of TB, then this is likely to be due to a particular mix of primary progression and reactivation disease.

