### Sample size

#### Prevalence in neighbourhoods

The community estimate of TB prevalence from the Indonesian National Prevalence Survey result for Java was 0.5% (95% CI 0.4 to 0.6%) [22]. We expect a higher rate among TB neighbourhoods, and pragmatically (to justify a policy change), a prevalence of approximately 1.25% culture positive TB cases will be needed in the neighbourhoods. With 4500 neighbourhood participants, the 95% confidence interval around 1.25% will be 0.9 to 1.6%, comfortably above the community estimate.

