## Discussion

The World Health Organization (WHO) 2020 Global TB Report showed Indonesia had the second highest TB incidence in absolute numbers [1]. In 2015, the National TB Program budget was estimated to be 133 million US dollars, much of which is unfunded [15]. This study will confirm whether neighbourhoods in the vicinity of routinely diagnosed TB index cases constitute a high-risk sub-population that may warrant active intervention to enhance TB control. Evidence provided will be crucial for the Indonesian TB Control Program in scaling up efforts towards the elimination of TB in a targeted and cost-effective way.

The combination of high precision genotyping, expanded social network questionnaires, and network analyses provides the opportunity to explore *Mtb* transmission. Genomic and social network analyses will provide important information to guide the design of possible interventions that may include active case finding, preventive treatment, and/or enhanced infection control measures in specific locations. For example, if ‘recent’ transmission of *Mtb* from index case households to neighbourhoods is indicated as explaining a large component of high neighbourhood prevalence, an intensive intervention of active case finding for early diagnosis and treatment would be warranted. If transmission ‘hotspots’ within the neighbourhoods can be identified, infection control measures could be considered. If high prevalence and incidence of TB is confirmed but there is a relatively low rate of genomic match within neighbourhoods, it may be that socioeconomic factors that promote reactivation are predominant. An intervention of screening for latent TB infection and initiation of preventive treatment to reduce the possibility of reactivation could be considered, or the focus could be on socioeconomic factors themselves, as suggested by WHO as part of the global strategy to End TB [23].

The proportion of TB cases that can be included in the analysis will be crucial to the ability to interpret these data. As COVID-19 continues to be prevalent in Indonesia, it is possible that recruitment and follow-up will be hindered with fewer than expected numbers being included in the study. This information will be closely monitored and every attempt made to follow-up participants through regular phone contact.

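### Neighbourhood prevalence is set against an external Java or Java/Bali survey figure across three TB definitions, so a result above it cannot by itself separate excess risk near a case from a higher local background

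*Protocol article*

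**What the plan says.** The sample-size section (Prevalence in neighbourhoods) takes its reference from a survey: "The community estimate of TB prevalence from the Indonesian National Prevalence Survey result for Java was 0.5" per cent, with a 95% CI of 0.4 to 0.6%. It sets a target tied to a policy change, "a prevalence of approximately 1.25% culture positive TB cases will be needed in the neighbourhoods", and reads the expected precision against the survey: "With 4500 neighbourhood participants, the 95% confidence interval around 1.25% will be 0.9 to 1.6%, comfortably above the community estimate".

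Outcome measures and statistical analysis plans the number, percentage and interval of "positive TB cases, according to each TB definition (definite, probable, possible), will be estimated", and continues: "These proportions will be compared between households, neighbourhoods, and estimates from the Indonesian National Prevalence Survey for Java/Bali". In that section:
- definite TB is culture or Xpert positive;
- probable TB is smear positive with symptoms and a suggestive x-ray, but culture negative or not done;
- possible TB rests on symptoms, x-ray or both, with all bacteriology negative or not done.

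Participants are aged 10 or more and live in six neighbouring health-centre areas of Bandung (Study design; Prospective cohort study).

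The Introduction gives a national prevalence of 647 per 100,000. From a Bandung feasibility study it gives self-reported incidence per 100,000 per year of 649 in household contacts, "675 in neighbouring households, and 325 in randomly selected neighbourhoods".

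The Discussion states the purpose: "This study will confirm whether neighbourhoods in the vicinity of routinely diagnosed TB index cases constitute a high-risk sub-population".

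**The concern.** The Discussion asks about people living near a known case. Answering that needs a reference for similar people not selected for living near one. The plan names two comparators. Index-case households are exposed and cannot supply a background. That leaves the survey, which differs from the study sample in ways visible in the article:

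- **Place.** Six adjacent urban areas of one city are set against Java in one section and Java/Bali in another.
- **Definition.** The 1.25% target is culture-positive TB. The comparison covers three categories: one adds Xpert, one rests on smear, and one has no positive bacteriology. The article gives a single survey figure, 0.5%.
- **Age.** The study excludes children under 10. The survey's age range is not given.

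At stake is the reading of a positive result. If Bandung as a whole has more TB than the survey stratum, neighbourhood prevalence could lie above the survey figure with no excess around index cases, and proximity could be credited with a city-wide difference.

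**Working it through.** **Inputs.** Survey figure 0.5% (95% CI 0.4 to 0.6%), target 1.25% and n = 4500, from the sample-size section; national prevalence 647 per 100,000 = 0.647%, from the Introduction. Bandung's own background prevalence is not in the article, so values from 0.5% to 1.0% are an assumed range.

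**1. The plan's interval.** Wald: p ± 1.96 × √(p(1 − p)/n).
√(0.0125 × 0.9875 / 4500) = 0.00166, and 1.96 × 0.00166 = 0.0032, so the interval is 0.93 to 1.57%. The stated 0.9 to 1.6% is reproduced; Wilson (0.96 to 1.62%) and Clopper-Pearson (0.94 to 1.61%) agree closely. The arithmetic is not at issue.

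**2. Smallest result whose interval clears the survey.** The lower limit first exceeds 0.5% at 34 cases (34/4500 = 0.76%) and first exceeds 0.6%, the survey's upper limit, at 40 cases (40/4500 = 0.89%).

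**3. How often that happens with no near-case excess.** Let neighbourhoods near cases have exactly the local background b, with X ~ Binomial(4500, b). The probabilities are P(X ≥ 34) and P(X ≥ 40). Independence is assumed, so household and neighbourhood clustering is ignored.

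| Local background b | Lower limit > 0.5% | Lower limit > 0.6% | Ratio if 1.25% is observed (1.25/b) |
|---|---|---|---|
| 0.5% (survey) | 1.4% | 0.1% | 2.5 |
| 0.6% (survey upper limit) | 11% | 1% | 2.1 |
| 0.647% (national figure) | 20% | 3% | 1.9 |
| 0.75% (assumed) | 51% | 16% | 1.7 |
| 0.9% (assumed) | 87% | 55% | 1.4 |
| 1.0% (assumed) | 96% | 79% | 1.25 |

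**4. Reading the table.** The article's own national figure lies above the survey interval of 0.4 to 0.6%, so its two benchmarks already differ. The ambiguity is greatest for results from 0.76% up to the target. If 1.25% is observed, a background of 0.647% still leaves a ratio of 1.9, and the background would have to reach about 0.93% to fall inside the study's own interval.

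**5. Definitions.** Their effect cannot be computed, because the survey's case definition and age range are not in the article. It can only be said that three different categories cannot all match one bacteriological survey estimate.

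**The case against.** Most of the counter-case limits the point without removing it.

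- **A reader might infer a formal test against the survey.** There is none. The sample-size text is a precision statement around 1.25%, with no pass rule. The key outcome is neighbourhoods compared with households, and the survey is a further reference. It is still the only reference that could stand for background.
- **A reader might infer that the study promises to find high risk.** The Discussion says it will confirm *whether* this is so, and its wording can be read as a statement about targeting, for which absolute prevalence is what matters. That stands. The limit concerns attributing the result to vicinity.
- **A reader might infer that every neighbourhood would exceed 0.5%.** This is false. There are 4500/250 = 18 people per neighbourhood, and at 1.25% about 0.9875^18 = 80% would have no case. Only the pooled proportion is informative.
- **A reader might infer that Bandung's background is high enough to explain 1.25%.** Nothing in the article supports 0.93% or more. The feasibility rates give 675/325 = 2.1. If that ratio carried over to prevalence (assumption), 1.25% near cases would imply a background of 1.25/2.08 = 0.60%, the upper edge of the survey interval. This points away from a purely city-wide explanation.
- **Mechanism is studied elsewhere.** Sequencing compares pairs within households, within neighbourhoods and across neighbourhoods, and the Discussion allows that high prevalence with few genomic matches may reflect socioeconomic factors. This bears on relatedness among cases. It supplies no background prevalence.
- **Standardisation may sit in an analysis plan that is not shown.** Agreed, and its absence from the article is not held against it. The plural word for the survey estimates also leaves room for definition-specific figures. But the two stratum labels, the three-category comparison and the culture-positive target are all stated in the article.
- **The rate of 325 might seem a ready local control.** It is self-reported incidence. The planned incidence comes from people screened at baseline, phoned about four-monthly and re-screened at 12 months. The two are not comparable, and the rate gives no prevalence reference.

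**Conclusion.** The point holds as a limit on inference and a mismatch of comparators. The stated interval is correct. The survey comparison, as described, cannot by itself separate excess risk near a case from a higher local background, and it carries two stratum labels and three case definitions against a culture-positive target.

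With no true near-case excess, the lower limit would exceed 0.5% in about 20% of studies at a background of 0.647% and about 51% at 0.75%. Against 0.6% the figures are 3% and 16%. These rest on independence between participants, on case definitions that match, and on background values that the article does not give for Bandung; 0.647% is a national figure used as an illustration. The documents do not show that Bandung's background is raised, nor the size or direction of any age or definition bias. The change should be made, but nothing here invalidates the study.

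**What to change.** 1. Name one survey stratum, the same in the sample-size section and in Outcome measures. Restrict the survey comparison to the study category that matches the survey's bacteriological definition and to the survey's age range. Standardise by age and sex (and to the urban stratum where published), and carry the survey's own confidence interval into the comparison. Do not compare possible TB with the survey.
2. State in Outcome measures and in the Discussion that the survey is an external benchmark: a higher result shows prevalence above that benchmark, which is relevant to targeting, and does not by itself establish excess risk due to vicinity.
3. Use the feasibility rate of 325 per 100,000 per year, if at all, as descriptive context labelled as self-reported incidence.

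**Cost.** A small standardisation step, some rewording and a more modest claim; no new participants. Isolating vicinity directly would need concurrently screened comparison neighbourhoods, which is a much larger change: for 1.25% against 0.647%, about 4055 people per group at 80% power and two-sided 5%, before any allowance for clustering. It is not asked for here.
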